### Secondary outcomes

Secondary outcomes will also guide the design of full trial processes, sample size calculations and outcome choice (by exploring impacts on patient-level and implementation measures) and ways to support the physiotherapists to deliver the intervention (by exploring determinants on implementation success). All secondary outcomes are listed in Tables 3 and 4. Patient-level outcomes will be assessed by a physiotherapist who has been trained in conducting the outcome measures and is blinded to group allocation.

### Data analysis

#### Sample size

##### Phase I

All physiotherapists working in the rehabilitation ward will be recruited as therapist-participants.

##### Phase II

A total of 30 Patient-participants (15 per group) will be recruited. The sample characteristics will be similar to the target population for the future large-scale implementation trial. We reasoned that this sample size would provide sufficient information to deem feasibility [21].

### Data management and analysis

Feasibility trial process measures and implementation outcomes will be collected using Excel spreadsheets and through other study documents (e.g., practice sheets). Patient-level data and implementation determinants questionnaire data will be entered into a study REDCap database with license held by the University of Sydney. Data analysis will be conducted using STATA statistical software. Most feasibility outcome measures will be descriptively presented using frequencies, total numbers, and percentages or proportions. The exception is the patient-level clinical trial outcomes and any feasibility outcome measures collected for both groups of phase II. These data will be analyzed using the intention-to-treat dataset. That is, all patients randomized into the study irrespective of adherence to interventions. Between-group comparisons for each of the continuously scored patient-level and implementation outcome measures will be made using linear models with baseline scores entered as a covariate. Fall rates in both groups will be descriptively presented.

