#### Patient-participants for phase II

All patients admitted to the rehabilitation ward will be screened against the eligibility criteria by the site coordinator, who will seek advice on patient eligibility from the multidisciplinary rehabilitation team as needed. Details will be recorded into a password protected screening log in Excel. Potential participants who may not be eligible at the first screening will continue to be screened during their inpatient stay and will be invited to participate in the study if subsequently found eligible. Patients who are eligible will be provided verbal information about the study. If the patient is interested in taking part in phase II of the trial, they will be provided with a written participant information sheet and consent form to read. All participants will provide informed written consent before recruitment into the study. Informed consent will be obtained by a researcher who is not responsible for the clinical care of the patient.

Patient-participants will be randomized to an intervention or control group after completion of baseline measures (including 24-h physical activity monitoring). Each participant will be assigned a study ID number and all future documents relating to a participant will use this study number. A variable block randomization schedule will be prepared using the Sampsi command in STATA v14 by a researcher not involved in patient recruitment. The randomization schedule will incorporate stratification for baseline mobility (SPPB score < 6 vs. ≥ 6) and health condition (neurological vs. non-neurological). The trial will use a centralized web-based randomization system stored on REDCap (Research Electronic Data Capture). This will ensure concealment of allocation to groups and an auditable process.

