a. Equipment	•Number and cost of devices + consumables/support equipment (e.g., data cards) •Number lost/broken devices needing replacement	Nil
b. IT	How many times devices did not work, time needed to fix, how and who it was fixed by and cost of fixing it	≥ 75% devices work for at least 75% of trial time
c. Staff	•Total FTE staff within the physiotherapy rehabilitation team that are participating in the trial •Number of physiotherapists needed training over course of project and number of hours spent training them in using digital devices •Number of physiotherapy students who required training (total blocks and total students) over course of project and number of hours spent training them in using digital devices •Number of training sessions missed by staff and students and reasons why •Number of staff trained and conducting screening, recruitment and outcome assessments	Nil
d. Training physiotherapists to embed digital devices	•Time and hours spent by clinical champion and study investigators in staff training •Number of workshops/journal clubs/clinical reasoning/audit and feedback activities performed	Nil
3.Management		
a. Dosage	•Percentage of exercise practice sheets reflecting usual care and digital device that are complete and legible with repetitions recorded (a **PRIMARY **outcome) •Number of devices that dosage data were successfully retrieved from •Who collected and how were dosage data collected for technology use?	•Exercise practice sheets complete for ≥ 85% of all participants
4. Patient- and implementation outcome measures		
a. Safety	•Number and type of minor and serious adverse events (e.g., falls) and circumstances of event when using digital devices during supervised/semi-supervised/out of therapy practice collected from hospital incidence reporting system	Nil
b. Estimation of effectiveness	•Between group difference and 95% CI for each patient-level outcome measure at 3 weeks post-randomization (these are outlined in Table 4)	Nil

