c. Success of implementation	•Fidelity: average total active time in minutes per day using digital devices for mobility tasks (a **PRIMARY** outcome) •Number of days over 3-week intervention technology not used by participants and reasons why (e.g., patient refusal, technology not working, staff shortages) •Device use: percentage of participants each device was used with; average number of different devices used per participant; percentage of devices used per participant where it was progressed (e.g., game level, repetitions, sets, time) •Type of practice: percentage of participants each mobility limitation was trained with devices; average number of different mobility limitations trained per participant •Percentage of staff trained that participated in prescribing and delivering rehabilitation using digital devices	Average of ≥ 30 min per day for > 50% intervention participants; 0 min per day for > 90% control participants (to confirm no contamination)
d. Determinants of implementation success	•Change in physiotherapists’ capability, opportunity and motivation to prescribing and delivering rehabilitation using digital devices, measured using study specific questionnaire (see Additional file 4), developed based upon the COM-B self-evaluation questionnaire [27]	Nil

The patient-level clinical trial outcomes include all the outcome measures that would be used in the future large-scale implementation trial. They are being collected at baseline and 3 weeks after randomization during phase II. If a patient is discharged before the scheduled 3-week assessment, every attempt will be made to collect all the patient-level measures prior to their discharge. The purposes of collecting these data are to ensure they are all suitable outcome measures for the future large-scale implementation trial and that they are all feasible to collect as well as to estimate the impact of the approach taken to guide future sample size calculations. They include measures of mobility, general health and function, quality of life, and physical activity. In addition, data on falls and adverse events will be collected over the 3-week intervention period (see Table 4).

**Table 4 Tab4:** List of patient-level clinical trial outcome measures collected during phase II. These data will be collected at baseline (pre) and 3 weeks (post) for all patient-participants

Outcomes	Pre	Post
Mobility		

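### The stated linear model names only the outcome's own baseline as covariate, leaving out both stratification factors, and its baseline term does not apply to device minutes

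*Protocol article*

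**What the plan says.** Under Recruitment and allocation (patient-participants for phase II), the randomisation schedule incorporates "stratification for baseline mobility (SPPB score < 6 vs. ≥ 6) and health condition (neurological vs. non-neurological"). Under Sample size, phase II: "A total of 30 Patient-participants (15 per group) will be recruited".

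Data management and analysis gives one model and its scope: "Between-group comparisons for each of the continuously scored patient-level and implementation outcome measures will be made using linear models with baseline scores" as the covariate. No other covariate is named.

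Table 3 (4b, estimation of effectiveness) lists the output: "Between group difference and 95% CI for each patient-level outcome measure at 3 weeks post-randomization". The Outcome measures section says these estimates are meant to guide future sample size calculations.

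Table 3 (4c) lists active minutes per day on digital devices as the fidelity measure and a primary outcome. Its criteria are at least 30 minutes per day for more than 50% of intervention participants, and 0 minutes for more than 90% of controls. The Primary outcomes section says it is taken from the practice sheets of both groups during phase II.

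**The concern.** Two statements in the article do not fit together well.

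- **Design and model.** Stratified allocation balances the groups on SPPB band and diagnosis, which lowers the true variance of the group difference when those factors are prognostic. A model without them leaves their effect in the residual, so the standard error does not reflect that gain. Health condition is in none of the stated models. SPPB is in the model only for the SPPB outcomes, and not for single leg stance, balance range, step test, AM-PAC, EQ-5D or step count. At stake is the precision of the differences that will inform the larger trial.
- **Model and outcome.** The sentence asks for a baseline score on implementation outcomes as well. Device minutes per day, the continuous one listed for both groups, has no value before randomisation.

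**Working it through.** **Inputs from the article:** 30 patients, 15 per group; two binary stratification factors; 80% of ward patients neurological.

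**Assumed, because the article gives no figure:** SPPB band split 50/50; baseline-outcome correlation 0.6, so residual SD √(1 − 0.6²) = 0.8 of the outcome SD before stratum effects; each factor shifts the outcome by d residual SDs beyond baseline; all 30 patients analysed. The sample size of 30 has no stated statistical inputs, so there is no figure to reproduce.

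**Step 1, degrees of freedom.** The stated model has 30 − 3 = 27 and the model with both factors 30 − 5 = 25. The t values are 2.052 and 2.060, a ratio of 1.004. That is the cost of adjustment, apart from a small loss from chance imbalance.

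**Step 2, stated model if the factors do not matter.** Half-width = t × √(2/15) × 0.8 = 2.052 × 0.365 × 0.8 = 0.60 outcome SD. Simulation gives 0.606 for the stated model and 0.614 with both factors added, so adjustment widens the interval by 0.614/0.606 − 1 = 1.3%.

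**Step 3, factors that do matter.** Left out, they add d² × (0.8 × 0.2 + 0.5 × 0.5) = 0.41d² to a residual variance of 1. The approximate width ratio, adjusted over stated, is 1.004 / √(1 + 0.41d²):

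- d = 0.25: 1.004/√1.026 = 0.99
- d = 0.5: 1.004/√1.103 = 0.96
- d = 0.8: 1.004/√1.262 = 0.89
- d = 1.0: 1.004/√1.41 = 0.85

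**Step 4, simulation with stratified blocks.** This also carries the cost of chance imbalance. The second column takes the outcome's baseline as independent of SPPB; the third gives them a correlation of 0.7.

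| d per factor | Independent of SPPB | Correlated 0.7 |
|---|---|---|
| 0 | 1–2% wider | 1–2% wider |
| 0.25 | no gain | no gain |
| 0.5 | about 4% narrower | about 2% narrower |
| 0.8 | about 10% narrower | 7–8% narrower |
| 1.0 | about 15% narrower | about 12% narrower |

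At d = 1.0 the mean half-widths are 0.722 (stated) and 0.614 (adjusted), a ratio of 0.85. Coverage of the stated model is about 95% when the factors do not matter and about 97% at d = 1.0. The departure from nominal is in the conservative direction.

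**Step 5, SPPB outcomes.** Their own baseline already carries most of the SPPB stratum, leaving mainly diagnosis unadjusted. Simulated width ratios are 1.022, 1.007, 0.981 and 0.926 for diagnosis effects of 0, 0.43, 0.71 and 1.14 residual SD. Even a very strong diagnosis effect therefore gives only about 7% narrowing.

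**Step 6, device minutes.** More than 90% of 15 controls means at least 14 should record 0. If the control variance is close to 0 and the intervention variance is s², the pooled standard error of the difference is √(s²/2 × 2/15) = s/√15. That is the standard error of the intervention mean alone, but credited with 28 degrees of freedom rather than 14. The comparison adds nothing to the intervention-arm mean, and there is no baseline score to enter.

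**The case against.** The strongest reply is that the article is condensed and the analysis plan is not shown. It names the baseline score as a covariate without saying it is the only one, and the plan may add the strata. That is a fair limit on the point, and nothing in the article excludes the factors. But the article does state a model, its covariate and its scope, and that statement should match the stratified design it describes.

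A second reply is that the gain is assumed. This stands: the article gives no stratum effect, and with small or null effects the gain disappears or reverses.

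A third is that little depends on it. Table 3 sets no feasibility criterion for estimation of effectiveness, and the patient-level effects are exploratory. This also stands, and keeps the point modest.

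A reader might infer that the implementation part also fails for the COM-B questionnaire, since Table 3 describes it as "Change in physiotherapists’ capability, opportunity and motivation to prescribing and delivering rehabilitation using digital devices" and therapists are not randomised. The documents do not support that. The Outcome measures section separates implementation outcomes from determinants, Table 3 puts the questionnaire under determinants (4d), and the data management text also calls it a determinants questionnaire. The model sentence covers implementation outcome measures, so it does not assign the questionnaire to a between-group model.

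**Conclusion.** The point holds in a limited form. The stated model does not name the two stratification factors, and adding them is a nearly free improvement. Under the assumptions listed, the intervals narrow by about 4% to 15% for effects of 0.5 to 1.0 residual SD per factor. They narrow less where the outcome's baseline overlaps with SPPB, not at all at 0.25, and they widen by 1–2% if the factors are not prognostic.

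Two stronger readings are tempting and should be resisted. One is that the intervals are simply too wide or wrong: that depends on prognostic strength, which the documents do not give, and the stated model keeps at least nominal coverage for patient-level outcomes. The other is that a primary outcome cannot be analysed: fidelity is judged by the Table 3 criteria, which need no model, so the unavailable baseline term is a wording problem that does not affect the feasibility decision.

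**What to change.** Revise the model sentence in Data management and analysis.

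- **Patient-level outcomes with a baseline:** fit group + own baseline + health condition + baseline SPPB (score or band). For the SPPB outcomes the baseline score already serves, so only health condition is added.
- **Baseline term:** limit it to outcomes that have a baseline.
- **Active device minutes per day:** summarise within the intervention arm against the Table 3 criterion, and report control use descriptively as contamination.

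The cost is a change of wording and at most two degrees of freedom (27 to 25; t from 2.052 to 2.060). No new data are needed, because both factors are recorded for randomisation.

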## Discussion

There is growing evidence to indicate that exercise prescribed using digital devices can improve mobility outcomes in people undertaking rehabilitation when provided in addition to usual care [22]. The AMOUNT rehabilitation trial provided further rigorous evidence of effectiveness for a tailored approach to selecting the most appropriate digital device and games to address patients’ mobility limitations while respecting their preferences and goals [9]. However, this intervention was delivered by research physiotherapists employed by study funds. It is yet to be determined if a similar tailored digital intervention can be delivered as an additional dose of exercise by physiotherapists employed in a public hospital with the usual staff available, and whether similar outcomes can be achieved. This feasibility study is the essential ground work recommended to inform the conduct of large-scale implementation trial to answer these question [11].

It is important to undertake implementation research to speed up the translation of research findings into practice. One estimate suggests that is takes 17 years to implement research into clinical practice [23]. Implementing evidence into clinical practice is challenging and can be influenced by factors such as lack of knowledge, skills and resources, competing demands of the clinician, and priorities of the service [24]. The need to test the feasibility of implementation strategies and understand the influences on implementation on a smaller scale first is crucial for determining potential for broader implementation and scale-up in the future [11]. This feasibility trial will therefore provide vital information about the feasibility of running a large-scale implementation trial of digital devices across rehabilitation services in other publicly funded hospitals.

A potential limitation of this study is the risk of contamination between control and intervention participants as the physiotherapists who receive the implementation strategies may inadvertently incorporate the digital devices into their therapy sessions for the participants in the control group. To address and monitor this risk, we will educate the physiotherapists on the risk of contamination and monitor the exercise practice sheets from both groups to ensure that the digital devices are only being prescribed to participants in the intervention group. A cluster or step-wedged trial design may be preferable for the future implementation trial to address this limitation [25]. Another potential limitation is the feasibility of delivering the education and training implementation strategies required to a team with staff who rotate every 3 months and have 5-week student placements. To address this, a physiotherapist employed in the rehabilitation team will work as the clinical champion on this study and provide ongoing training to new staff and students as required. In addition, all education sessions will be recorded so new staff and students can view them at their convenience. A final potential limitation is the requirement of accurate recording of dosage data for both groups in the study, with dosage of practice identified as the likely primary implementation outcome for the future large-scale implementation trial. To address this, procedures for recording dosage have been created. We will audit and provide feedback to physiotherapists on their documentation and recording of dosage in the exercises practice sheets. In addition, recording of dosage will be evaluated as a primary outcome of this feasibility study.

A strength of this study is that the protocol has been developed considering current best practice guidance in both feasibility and implementation fields [11, 26]. The use of the hybrid design has the advantage that it will test both implementation and intervention in the same trial, which reduces the time required to test both separately and accelerates the implementation process [10]. This trial will provide important information about the feasibility of physiotherapists implementing exercises using digital devices in a busy public hospital setting. It will also provide important information on the suitability of the implementation strategies to train and support clinical physiotherapists to embed digital devices in a rehabilitation setting. This study is the critical first step to the design and future conduct of a large clinical trial to implement exercises using digital devices in rehabilitation.

## Data Availability

De-identified patient-level data will be available to other researchers on request to Chief Investigator when the main study results are published.

## Abbreviations

AMOUNT: Activity and MObility UsiNg Technology
COM-B: Capabilities, Opportunities, Motivation-Behaviour
ANZCTR: Australian and New Zealand Clinical Trial Registry
COVID-19: COronaVIrus Disease of 2019
USA: United States of America
LLC: Limited Liability Company
CONSORT: CONsolidated Standards Of Reporting Trials
SPIRIT: Standard Protocol Items: Recommendations for Interventional Trials
TIDieR: Template for Intervention Description and Replication
SPPB: Short Physical Performance Battery
MMSE: Mini-Mental State Examination
MoCA: Montreal Cognitive Assessment
REDCap: Research Electronic Data Capture
ERIC: Expert Recommendations for Implementing Change
